#### Secondary outcomes

2.9.2

Menstrual cycle characteristics will be evaluated using two measures: 1) mean menstrual cycle length, calculated as the total number of days in the observation period (84 days for the 12-week treatment period, and 84 days for the 12-week follow-up period) divided by the number of menstrual cycles that occurred during that period. A menstrual cycle is defined as the interval from the first day of one menstrual bleeding to the day before the next menstrual bleeding. If no menstrual bleeding occurs during the entire observation period, the mean cycle length is considered missing, and the participant will be classified as having amenorrhea for that period. This value will be derived from participant-maintained calendars, and the average during treatment and follow-up will be compared to the self-reported baseline.; and 2) the menstrual cycle recovery rate, defined as the proportion of participants achieving a normalized cycle length of 21–35 days.

The sex hormone profile, measured in the early follicular phase (days 2–5 of a spontaneous cycle), includes the Free Androgen Index (FAI) (calculated as [total testosterone/sex hormone-binding globulin (SHBG)] × 100) (30) and the LH/FSH ratio.

The metabolic profile comprises three domains: 1) Anthropometric measures: body weight, height (for BMI), waist circumference (WC), and hip circumference (HC) to calculate the waist-to-hip ratio (WHR); 2) Glucose metabolism: fasting plasma glucose (FPG) and fasting insulin (FINS), with insulin resistance estimated by the Homeostatic Model Assessment index (HOMA-IR), a marker of insulin resistance, is calculated as (FINS × FPG)/22.5 (31); 3) Lipid profile: Total cholesterol (TC), triglycerides (TG), high-density lipoprotein cholesterol (HDL-C), and low-density lipoprotein cholesterol (LDL-C).

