### Concomitant medication

2.8

To ensure patient safety and standardize clinical management during the trial, the use of concomitant medication will be permitted and recorded under the following specific circumstances:

Rescue Medication for Prolonged Amenorrhea: If a participant experiences amenorrhea for more than 90 days during the trial period, oral dydrogesterone (10 mg, once daily for 10 days) may be administered to induce withdrawal bleeding. All rescue interventions will be thoroughly documented within the designated rescue medication section of the case report form (CRF).Pre-existing chronic medications unrelated to gynecology or fertility management (e.g., agents for hypertension, hypothyroidism) may be continued throughout the trial, provided the site investigator confirms no interference with trial outcome evaluation. Full details of all concurrent medications—including drug name, dosage, administration frequency, and clinical indication—must be recorded comprehensively in the Concomitant Medication module of each participant’s case report form (CRF).

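### The Week 24 menstrual outcomes have no rule separating bleeds induced by the rescue drug from spontaneous ones

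*Protocol article*

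**What the plan says.** Section 2.8 (Concomitant medication) sets the trigger: "If a participant experiences amenorrhea for more than 90 days during the trial period, oral dydrogesterone" for 10 days "may be administered to induce withdrawal bleeding". Use is optional, and each course is recorded in its own part of the CRF.

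Section 2.9.2 (Secondary outcomes) divides the days in the observation period ("84 days for the 12-week treatment period, and 84 days for the 12-week follow-up period") by the number of cycles. It defines a cycle thus: "A menstrual cycle is defined as the interval from the first day of one menstrual bleeding to the day before the next menstrual bleeding". The source is the participant's own calendar. On absence of bleeding it says: "If no menstrual bleeding occurs during the entire observation period, the mean cycle length is considered missing", and she is then classed as amenorrhoeic. Recovery is "the proportion of participants achieving a normalized cycle length of 21–35 days"; whether that length is the period mean or a single interval is not said.

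The same section requires a spontaneous cycle for hormone sampling but makes no such restriction for the cycle outcomes. Section 2.13 analyses secondary outcomes on available data and has no rule for women who received rescue.

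**The concern.** The rescue drug is given in order to produce a bleed, and the outcome is a count of bleeds. The calendar rule has no step that tells the two kinds apart, so whoever derives the outcome from calendars would probably count an induced bleed by default.

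The women affected are those with the longest amenorrhoea, whom the amenorrhoea class is meant to identify. Because rescue is optional, two women with the same natural history could be classified differently only because one was given the drug. The follow-up recovery rate and amenorrhoea class would then partly reflect rescue use, which may differ between arms.

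**Working it through.** The plan gives no figure for rescue use or amenorrhoea, so there is nothing of its own to reproduce on this point. The sample size does not enter.

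**1. When rescue can happen.** Inputs: treatment starts 2–4 days from the onset of a spontaneous period (section 2.7); treatment lasts 84 days (section 2.9.2); the trigger is more than 90 days (section 2.8).

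- Depending on how the onset day is counted, treatment day 1 is cycle day 2 to 5, and the first day past the trigger is cycle day 91 or 92.
- Treatment day of trigger = trigger cycle day − starting cycle day + 1. Earliest: 91 − 5 + 1 = 87. Latest, for a woman with no further bleed: 92 − 2 + 1 = 91.
- Less 84, this is follow-up day 3 to 7. No rescue can fall in the treatment period.

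**2. When the induced bleed falls.** Assumption, not in the documents: the bleed starts 2–7 days after the last tablet. The last tablet is on trigger day + 9, so for a woman with no bleed since treatment start the induced bleed falls between follow-up day 3 + 9 + 2 = 14 and 7 + 9 + 7 = 23.

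**3. What else can happen in follow-up.**
- A trigger by study day 168 needs a last bleed by about day 168 − 90 = 78, before follow-up opens on day 85. A rescued woman therefore has no spontaneous follow-up bleed before her rescue.
- Two induced bleeds are at least about 90 + 10 = 100 days apart, so at most one fits into 84 days.

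**4. Effect on the derived values.** Mean length = 84 / number of cycles, counting one cycle per bleed. This is an assumption, but it fits the rule that the value is missing only when there is no bleed at all. Recovery is judged here on that mean.

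| Spontaneous bleeds in follow-up | Induced bleed counted | Not counted |
|---|---|---|
| 0 | 84/1 = 84, not recovered | missing, amenorrhoeic |
| 1 | 84/2 = 42, not recovered | 84/1 = 84, not recovered |
| 2 | 84/3 = 28, recovered | 84/2 = 42, not recovered |
| 3 | 84/4 = 21, recovered | 84/3 = 28, recovered |

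The amenorrhoea class changes in the first row and recovery in the third. If recovery were judged on single intervals, one spontaneous bleed 21–35 days after the induced one would be enough.

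**5. Direction for mean length.** In the first row, counting the bleed keeps the woman in the available-data ANCOVA at 84 days, the longest value the formula can give; not counting it drops her. In the next two rows, counting shortens her value. The net direction is not determined.

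**The case against.** - **The protocol does not say that induced bleeds count.** This is correct. A reader might infer that it does, but it is silent. It speaks of withdrawal bleeding in section 2.8 and menstrual bleeding in section 2.9.2, and records rescue separately. The distinction could have been intended, but no derivation rule states it.
- **Handling of rescue commonly belongs in the SAP.** This is fair in general. Here, though, the article itself fixes the observation days, the cycle definition, the amenorrhoea rule and the missing-value rule, and that definition collides with section 2.8.
- **Rescue alone does not make a woman recovered.** This stands under the 84/n mean. She needs two further spontaneous bleeds in the days left, 84 − 14 = 70 to 84 − 23 = 61 for a woman with no bleed since treatment start. Those intervals then average at most 35 to 30.5 days, so she is not plainly a hidden treatment failure.
- **The sustainability analysis is unaffected.** This stands. A reader might infer that failures are hidden in the test of lasting effect, but section 2.13 bases that test on the ultrasound-based COR at Weeks 12 and 24.
- **Few women may be affected.** This stands. Entry requires 35–60-day cycles over 12 months, and rescue is optional.
- **Simply not counting the bleed has a cost.** It would make a woman with no spontaneous bleed missing for mean length. This stands and shapes the fix.

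**Conclusion.** The gap is real but confined to the menstrual secondary outcomes in follow-up. The primary COR, the COR sustainability model and the treatment-period cycle outcomes are untouched.

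For each woman rescued, a counted bleed removes the amenorrhoea class (84 days instead of missing) and, with two later spontaneous bleeds, changes 42 days to 28 days and so not recovered to recovered. Only the single-interval reading, which section 2.9.2 leaves open, lets one later bleed suffice.

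The effect on the comparison between arms cannot be sized, because the documents give no rescue rates. A general pull toward no difference is therefore not shown, and for mean length the direction is uncertain. The timing conclusion follows from the protocol's own dates. The table assumes one cycle per bleed, and the dates of induced bleeds assume 2–7 days after the last tablet.

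**What to change.** In section 2.9.2, as an analysis rule only:

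- State that a bleed starting during a rescue course, or within a fixed interval after it (identified from the CRF), is not a menstrual bleed and neither starts nor ends a cycle.
- Apply the amenorrhoea class to spontaneous bleeds only.
- Count rescued women as not recovered in the follow-up recovery rate, in both arms.
- State whether recovery uses the 84/n mean or single intervals.
- For mean length, do not let rescued women drop out as missing. Keep them at a long value, for example 84 days or a worst rank, and add a sensitivity analysis.
- Report rescue use by arm.

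The cost is a few lines of text; rescue use is already collected. Week 24 menstrual results may look slightly less favourable. Other rules for rescued women are defensible, but one must be fixed in advance. The rescue rule itself is not addressed here.

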### Statistical analysis

2.13

All analyses will adhere to the Intention-to-Treat (ITT) principle. The baseline characteristics will be summarized descriptively by group using means (standard deviations) or medians (interquartile ranges) for continuous variables and frequencies (percentages) for categorical variables to assess between-group comparability.

For the primary outcome, the cycle ovulation rate (COR) at Week 12, any missing data will be handled using multiple imputation by chained equations (MICE) with 20 imputed datasets, and results combined using Rubin’s rules (35). The COR will be compared between groups using a linear mixed-effects model with study center as a random effect. The result will be presented as the mean difference between groups with its 95% confidence interval. As a sensitivity analysis, a per-protocol (PP) analysis will be performed, including only participants who completed the 12-week intervention with adequate adherence (defined as receiving ≥80% of the scheduled acupuncture sessions) and without major protocol violations.

To assess the sustainability of the treatment effect, the COR at Week 12 and Week 24 will be analyzed together using a linear mixed-effects model for repeated measures, including group, time point (Week 12, Week 24), and group-by-time interaction as fixed effects, with study center and participant as random effects (36).

The analyses for secondary outcomes will be conducted using available data. Continuous outcomes will be analyzed using Analysis of Covariance (ANCOVA), adjusting for corresponding baseline values and study center (37). Binary outcomes will be analyzed using generalized linear mixed models, incorporating study center as a random effect (38). All statistical tests will be two-sided, and a p-value < 0.05 will be considered statistically significant. All analyses will be performed using SAS software (version 9.4, SAS Institute Inc., Cary, NC, USA).

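### Women with no menses in an 84-day period are set to missing and drop out of the mean cycle length comparison, although their outcome is known and is the worst possible

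*Protocol article*

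**What the plan says.** Section 2.9.2 (Secondary outcomes) computes mean cycle length as 84 days divided by the number of cycles, separately for treatment and follow-up. It then adds: "If no menstrual bleeding occurs during the entire observation period, the mean cycle length is considered missing". In the same sentence it gives these women a status: "the participant will be classified as having amenorrhea for that period". No listed outcome or analysis uses that status.

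The second menstrual measure is "the menstrual cycle recovery rate, defined as the proportion of participants achieving a normalized cycle length of 21–35 days". Nothing is said about where a woman with amenorrhea falls in it.

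Section 2.13 (Statistical analysis) opens with "All analyses will adhere to the Intention-to-Treat (ITT) principle". For the primary outcome, "any missing data will be handled using multiple imputation by chained equations (MICE) with 20 imputed datasets". For the rest, "The analyses for secondary outcomes will be conducted using available data", and "Continuous outcomes will be analyzed using Analysis of Covariance (ANCOVA), adjusting for corresponding baseline values and study center".

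Section 2.8 (Concomitant medication) foresees amenorrhea of more than 90 days. It allows a drug that "may be administered to induce withdrawal bleeding", with its use documented in a rescue section of the case report form.

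**The concern.** A calendar that shows no bleeding for 84 days is an observation. The protocol recognises this by classifying the woman as amenorrheic, yet for cycle length it treats her as if nothing were known. Together with the available-data rule, this selects the analysis set on a post-randomisation outcome and always removes the same end of the distribution. A woman with one cycle scores 84 days. A woman with none, who is worse, scores nothing.

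Long gaps between menses reflect the ovulatory dysfunction that the treatment is meant to improve, so unequal amenorrhea between arms is plausible. The cycle-length comparison would then favour the arm with more amenorrhea. If MA reduces amenorrhea, part of its benefit is hidden. If MA has more of it, MA is flattered.

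**Working it through.** **The plan's own figures.** The protocol states no figure for the menstrual outcomes. Its sample size is for the primary outcome and reproduces: 65% versus 40%, two-sided 0.05, 80% power, chi-square without continuity correction, gives 62 per group; 62 / (1 − 0.20) = 77.5, rounded up to 78; total 156. It is not affected by this point.

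**What the formula can return.** 84 / number of cycles gives 84, 42, 28 and 21 days for one, two, three and four cycles. With zero cycles it is undefined. The true interval is then at least 84 days, so 84 is a lower bound.

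**Who leaves the analysis.** No bleeding in the period means cycle length is missing (2.9.2). Secondary outcomes use available data and imputation is named only for the cycle ovulation rate (2.13). The woman is therefore absent from the cycle-length ANCOVA.

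**Size.** Inputs, all assumed because the documents give none:
- mM, mS: mean cycle length among menstruating women in each arm
- aM, aS: share with amenorrhea in each arm
- amenorrhea valued at 84 days
- covariate adjustment ignored

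Available-data difference (SA − MA) = mS − mM.

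All-women difference = [(1 − aS)·mS + aS·84] − [(1 − aM)·mM + aM·84].

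With mM = 42 and mS = 50, the available-data difference is 50 − 42 = 8.0 days whatever the shares.

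- Amenorrhea 3% MA, 10% SA: SA = 0.90 × 50 + 0.10 × 84 = 53.40; MA = 0.97 × 42 + 0.03 × 84 = 43.26; difference 10.1 days. The available-data figure is too small by 2.1 / 10.1, about 21%.
- Amenorrhea 10% MA, 3% SA: SA = 0.97 × 50 + 0.03 × 84 = 51.02; MA = 0.90 × 42 + 0.10 × 84 = 46.20; difference 4.8 days. The available-data figure is too large by 3.2 / 4.8, about 66%.

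**Range when menstruating women do not differ** (both 42 days). The available-data difference is 0. The all-women difference, MA − SA, is 42 × (aM − aS):

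| Amenorrhea MA / SA | All-women difference (days) |
|---|---|
| 0% / 5% | −2.1 |
| 2% / 10% | −3.4 |
| 5% / 15% | −4.2 |
| 5% / 20% | −6.3 |
| 10% / 10% | 0 |
| 15% / 5% | +4.2 |

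An imbalance of 5 to 15 percentage points thus moves the comparison by about 2 to 6 days. With equal shares and equal means nothing changes. With equal shares and means 8 days apart, the change is only 8 × share, or 0.8 days at 10%.

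**Recovery rate, conditional only.** Suppose recovery were derived from the missing cycle length and these women were dropped. With assumed rates of 40% (MA) and 30% (SA) of all women and amenorrhea of 5% and 15%, the result is 0.40 / 0.95 = 42.1% versus 0.30 / 0.85 = 35.3%, a difference of 6.8 points instead of 10. If they count as not recovered, it stays at 10.

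**The case against.** The ratio has no value when the number of cycles is zero, so leaving it empty is understandable, and available-data analysis of secondary outcomes is common. That explains the rule but does not rescue it: the value is absent because of the outcome, not because observation failed.

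The number of women affected may be small. Entry requires cycles of 35 to 60 days over the preceding 12 months, and treatment starts just after a menses, so having no new menses in 84 days means a cycle at least 24 days beyond the longest eligible one. This stands as a limit on size. The share is unknown but not negligible by the protocol's own lights, since section 2.8 plans for more than 90 days without menses. The overstated case (10% MA, 3% SA) also needs MA to shorten cycles among menstruating women while raising amenorrhea. The scenario in line with the trial's hypothesis works against MA.

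A reader might infer that both menstrual outcomes lose these women. The text does not support that. The missing rule covers mean cycle length only, recovery is a proportion of participants, and a woman classified as amenorrheic most naturally counts as not recovered. Her removal is one possible reading.

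A reader might also infer that an induced withdrawal bleed counts as a menses and makes a rescued woman look improved. The protocol does not say so. Its cycle definition neither includes nor excludes such bleeds, and rescue use is recorded separately.

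**Conclusion.** The point holds for mean cycle length. The stated rule and the available-data analysis together exclude women with the worst observed result, contrary to the intention-to-treat statement. The difference between arms is biased towards the arm with more amenorrhea.

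In the illustration, 8.0 days is reported where keeping all women gives 10.1 or 4.8 days, depending on which arm has the excess. These figures rest on assumed means and amenorrhea shares and on the 84-day lower bound. They show direction and order of magnitude and are not a forecast.

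For the recovery rate and for induced bleeds the finding is only that the handling is unstated. This is a secondary outcome: the primary analysis and sample size stand. It should be corrected before unblinding, so that the handling cannot depend on the results.

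**What to change.** In section 2.9.2, stop treating amenorrhea as missing. Reserve that term for women whose calendar was not kept or who left the study.

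- Analyse cycle length so that these women are kept: for example a worst-rank analysis, censoring at 84 days, or the number of menses per 84 days with zero as a valid value. Name one in advance.
- Report the proportion with amenorrhea by arm for each period.
- State that women classified as amenorrheic count as not recovered and stay in the recovery-rate denominator.
- In the outcome definition, count only spontaneous bleeds as menses, identifying induced ones from the rescue records in the case report form.

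The cost is a change of wording and of one model. No new data are needed. The downside is that the result reads less directly as a mean number of days. The available-data mean among menstruating women can still be shown as a description.

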**Figure 1 f1:**
[figure not shown]
Flow diagram of the trial. PCOS, polycystic ovary syndrome; MA, manual acupuncture; SA, sham acupuncture; ITT, intention-to-treat; PP, per-protocol.

**Table 1 T1:** Schedule of enrollment, interventions, and assessments.

Study period	Screening	Baseline (Week 0)	Intervention (Weeks 1-12)	Post-treatment (Week 12)	Follow-up (Week 24)
Enrollment					
Eligibility Screening	X				
Informed Consent	X				
Randomization		X			
Interventions					
Manual Acupuncture			3 sessions/week		
Sham Acupuncture			3 sessions/week		
Assessments					
Cycle Ovulation Rate				X	X
Menstrual Calendar*	X	X		X	X
Reproductive Hormones (FAI, LH/FSH)		X		X	X
Metabolic Parameters		X		X	X
Anthropometrics (BMI, WC, HC, WHR)		X		X	X
Questionnaires (PCOSQ, SAS, SDS)		X		X	X
PGIC				X	X
Adverse event			Each visit	X	X
Blinding Assessment				X	
Adherence to treatment				X	X

BMI, body mass index; FAI, free androgen index; FSH, follicle-stimulating hormone; HC, hip circumference; LH, luteinizing hormone; PCOSQ, Polycystic Ovary Syndrome Quality of Life Questionnaire; PGIC, Patient Global Impression of Change; SAS, Self-Rating Anxiety Scale; SDS, Self-Rating Depression Scale; WC, waist circumference; WHR, waist-to-hip ratio.

*At Screening, participants recall their menstrual patterns over the prior 12 months to confirm eligibility (cycle length consistently between 35 and 60 days). At Baseline (Week 0), a paper calendar is provided for prospective daily recording thereafter.

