### Inclusion criteria

2.3

Participants will be women diagnosed with polycystic ovary syndrome (PCOS) according to the 2003 Rotterdam criteria (4), after the exclusion of other potential causes of hyperandrogenism or anovulation (e.g., thyroid dysfunction, hyperprolactinemia, congenital adrenal hyperplasia, androgen-secreting tumors). Eligible participants must meet all of the following criteria: (1) aged 21–40 years old; (2) maintained spontaneous menstrual cycles (without hormonal ovulation induction) over the preceding 12 months, with consistent cycle lengths ranging from 35 to 60 days; and (3) provision of written informed consent.

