Central to the intervention is a standardized yet flexible acupuncture protocol, built upon the TCM principles of tonifying the Kidney and regulating the Chong and Ren meridians. It is implemented through a fixed core set of acupoints (e.g., CV4, BL23, SP6, KI3) for consistent treatment, supplemented with adjunct points to accommodate individual TCM pattern presentations in PCOS. This design strikes a balance between methodological rigor and personalized clinical application. The active intervention is compared against a sham acupuncture procedure using non-acupoint, shallow needling, designed to provide a credible control for non-specific effects while maintaining participant blinding. This sham procedure was selected to balance methodological rigor with practical feasibility across the six participating centers.

Beyond these general quality measures, the primary methodological innovation is the proactive management of clinical heterogeneity. Recognizing that PCOS encompasses distinct phenotypes with potentially divergent treatment responses, this trial applies stringent inclusion criteria. By enrolling only women with spontaneous menstrual cycles of 35–60 days and excluding those with a BMI ≥28 kg/m², we aim to create a more homogeneous cohort characterized by mild-to-moderate ovulatory dysfunction. This deliberate population refinement seeks to minimize phenotypic confounding and provide a clearer signal of the intervention’s specific efficacy.

Our population selection was guided by methodological considerations to enhance internal validity. Women with BMI ≥28 kg/m² were excluded according to the Chinese obesity criteria (37), and those with spontaneous menstrual cycles of 35–60 days were enrolled based on the definition of irregular menstrual cycles in the 2023 International PCOS Guideline (4), defining a subgroup with mild-to-moderate ovulatory dysfunction.

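### A 35-day cycle satisfies both the entry range and the recovery range, so a woman with consistent 35-day cycles already meets the recovery definition at entry

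*Protocol article*

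**What the plan says.** **Entry.** Section 2.3 of the protocol article requires spontaneous cycles over the preceding 12 months "with consistent cycle lengths ranging from 35 to 60 days". The footnote to Table 1 repeats this as "cycle length consistently between 35 and 60 days" and says that the information comes from recall at screening. The Discussion presents the range as one of irregular cycles, "based on the definition of irregular menstrual cycles in the 2023 International PCOS Guideline".

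**Outcome.** In section 2.9.2 the menstrual cycle recovery rate is "defined as the proportion of participants achieving a normalized cycle length of 21–35 days". The sentence does not ask for a change from baseline. It also does not say whether the period mean, the last cycle or any single cycle is to be classified.

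**On-study derivation.** The only on-study derivation of cycle length, also in section 2.9.2, is the mean. Its numerator is the length of the period, 84 days each for treatment and follow-up, and this is "divided by the number of menstrual cycles that occurred during that period". A cycle is "the interval from the first day of one menstrual bleeding to the day before the next menstrual bleeding". How a cycle that straddles the start or end of a period is counted is not stated.

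**Analysis.** Section 2.13 adjusts continuous secondary outcomes for their baseline value. For binary outcomes it names a mixed model with center as random effect and no baseline term.

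**The concern.** The protocol treats 35 days as irregular when it admits a woman and as normalized when it scores her. With both limits inclusive and no change required, a woman can satisfy the recovery definition on the day she enters. For her the outcome would not measure recovery.

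If such women are scored as responders, they are so in both arms whatever the treatment does. That raises the sham rate and narrows the difference between arms. Baseline length is recalled while on-study length comes from a prospective calendar, so for a woman near the limit the method of recording alone could also move her across it.

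**Working it through.** **Plan's own figure (used only for the 78 per arm).** Inputs from section 2.12: 65% versus 40%, two-sided alpha 0.05, power 80%, 20% dropout. The pooled-variance formula without continuity correction is

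n = [1.96 × √(2 × 0.525 × 0.475) + 0.842 × √(0.65 × 0.35 + 0.40 × 0.60)]² / 0.25² ≈ 61.4, rounded up to 62.

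Then 62 / (1 − 0.20) = 77.5, rounded up to 78. Both figures reproduce.

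**Step 1: overlap of the ranges.** In whole days, entry is {35, …, 60}, which is 60 − 35 + 1 = 26 values. Recovery is {21, …, 35}. They share exactly one value, 35. If either bound at 35 were strict, they would share none.

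**Step 2: what the stated mean can yield.** With k cycles in 84 days the mean is 84/k:

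| k | 1 | 2 | 3 | 4 | 5 |
|---|---|---|---|---|---|
| Mean (days) | 84 | 42 | 28 | 21 | 16.8 |

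A value of 35 cannot occur. Recovery on this mean is simply k = 3 or k = 4.

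**Step 3: a woman whose 35-day cycles do not change.** Section 2.7 starts treatment 2 to 4 days into a spontaneous period. Take treatment day 1 as cycle day 2, 3 or 4. The next onsets then fall on treatment days 35, 34 or 33 and on days 70, 69 or 68. The following one (day 105, 104 or 103) is beyond day 84.

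| What is classified | k | Value (days) | Recovered? |
|---|---|---|---|
| 84/k, bleed onsets in the period | 2 | 42 | No |
| 84/k, cycles that end in the period | 2 | 42 | No |
| 84/k, cycles wholly inside the period | 1 | 84 | No |
| 84/k, every cycle that overlaps the period | 3 | 28 | Yes |
| Actual calendar cycle length | – | 35 | Yes |

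The follow-up period (days 85 to 168) gives the same five answers. Under the overlap count, unchanged cycles of 35 up to 42 or 43 days would also pass in the treatment period, so that reading goes well beyond the boundary value.

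**Step 4: possible size, under assumptions.** The documents give no distribution of cycle length. If each woman had one recalled whole-day length, spread evenly over the 26 values, the share at 35 is f = 1/26 = 3.8%, and 0.038 × 78 = 3.0 women per arm. If these women respond in both arms, they add nothing to the contrast, so the observed difference is d × (1 − f), where d is the difference among the others. For an assumed d of 20 points this is 20 × 0.962 = 19.2 points. If recall were to heap on five weeks, with f assumed at 10% or 20%, it would be 18 or 16 points.

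**The case against.** A reader might infer that women at the limit are counted as responders under the plan as written, and that this holds for any proper measure of cycle length. The documents do not support that. On the only on-study derivation given, such a woman scores 42 or 84 under three of the four ways of counting and is not recovered. She becomes a responder only if partial cycles are counted or if actual cycle length is classified, and section 2.9.2 states neither.

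A reader might also infer that many women are affected. That is not shown either. Eligibility applies the floor to cycles consistently, so a woman's average can equal 35 only if every cycle was 35 days. The even spread, the heaping shares of 10% to 20% and the 20-point difference are all assumptions. Nor is there a bias in favor of acupuncture: boundary responders would arise in both randomized arms alike.

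That a 36-day woman needs only a one-day change is true of any cut-point, and mean cycle length is also analyzed as a continuous outcome with baseline adjustment.

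The objection correctly adds that lowering the upper limit to 34 days does nothing by itself under 84/k, because 28 and 21 pass either way.

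What the objection does not remove is the shared value. The text places 35 days in both ranges and requires no change, and the open question of which length is classified is what prevents the reader from ruling out its effect.

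**Conclusion.** The contradiction is real and limited. A woman with consistent 35-day cycles meets the recovery criterion at entry. She counts as a responder without change if actual calendar length is classified, or if every overlapping cycle is counted in 84/k. She does not if the mean rests on bleed onsets or on completed cycles.

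The number of women concerned cannot be derived from the protocol. About 4%, or 3 of 78 per arm, holds only for the assumed even spread, and with an assumed true difference of 20 points it would cost less than one point. The consequence is a small dilution of one secondary outcome in both arms. The primary outcome and the sample size are not touched. The point merits a correction because it is cheap and because the endpoint should not be satisfied at baseline.

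**What to change.** 1. In section 2.9.2, reconcile the two ranges so that they share no value, by making one bound at 35 days strict. Changing the outcome bound leaves eligibility untouched. It is better written as below 35 days than as up to 34, since a mean of several cycles can fall between the two.
2. In the same sentence, apply the recovery criterion to actual calendar cycle length instead of 84/k, and state which cycles enter it and how those that straddle a period boundary are treated. Step 1 has no effect without this.
3. In section 2.13, add baseline cycle length as a covariate in the binary model for recovery. The value is already collected at screening.

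Do not keep the 21 to 35 range and bar 35-day women from counting as recovered. They would stay in the denominator as automatic non-responders even if their cycles shortened to 28 days, which replaces one misclassification with another.

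Cost: one bound, one clarifying clause and one covariate, and a slightly lower recovery rate in both arms.
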